### Data collection

#### Hospital data

Provider data will be gathered using standardised hospital/provider questionnaires for both control and intervention arms in RCT1 and RCT2. Data will be collected from 31 hospitals (30 in RCT1 and 29 in RCT2) from all seven sites (four hospitals in Bangladesh, five in Ethiopia, six in India Himachal Pradesh and the National Capital region, six in India Uttar Pradesh, three in Nigeria, five in Pakistan, and two in Tanzania) where YI are enrolled for treatment under RCT1 and/or RCT2.

Provider data for CEA will include the following variables:

Coverage of sick YIs (SYI) assessed, enrolled and treated under both RCT1 and RCT2 for control and intervention.Data on two outcome variables for all SYI covered under different treatment arms. Well-trained independent outcome assessor visits all enrolled cases on days two (only for RCT1), four, eight, and 15 after the initiation of treatment to assess the study outcomes in both intervention and control arms.Average annual salaries of nurses, paediatricians, medical officers and any other staff supporting treatment. To calculate staff costs per minute, data will be collected on the average number of days in a month and the average number of hours in a day that staff work.Staff time will be considered only for activities that are linked to hospital staff and not those linked to research staff, such as outcome assessment or treatment documentation (**Table 1**, **Table 2**). The activities for the staff time will be based on a pre-defined implementation strategy [21,22].Data will be collected for SYI that receive at least 80% of the treatment (recommended treatment) and those who receive <80% of seven-day (<5.5 days) treatment (partial treatment). The latter occurs due to a treatment failure, a change in treatment, readmission, left voluntarily, or death. For the recommended treatment, we will collect costs for the seven-day treatment period following the initial assessment, across both study arms and both trials. For partial treatment, medical costs will be calculated for an average treatment period of three days in RCT1 after the initial assessment, and for two days in RCT2 in both inpatient and outpatient arms after randomisation. Costs for enrolled SYI will be weighted by the proportion of participants receiving 80% recommended treatment and those receiving partial treatment, with weights set to SYI for each group. This prevents any child randomised and enrolled from being missed. Costs due to complications, changes in treatment, and/or readmission are outside the seven-day recommended treatment window in both study arms of both trials and will not be collected.Data on staff time per visit for an activity and the number of visits undertaken for each activity during the recommended treatment period will be collected by interviewing at least 3–5 staff of each type at each hospital.The staff time for all visits during the treatment period will be weighted by the number of days an infant receives the activity and the number of YI receiving the activity (defined as weighted by infant days). For the first activity assessment on presentation at the hospital, the number of SYI will be all enrolled for a given treatment, whether partial or recommended. For all other activities, SYI who receive 80% recommended treatment will be considered to have received seven days of treatment, and those receiving partial treatment for an average of three days to calculate the costs for those enrolled.The average exchange rate used to convert all the cost estimates in local currency into USD will be for 2024, the period for which the salaries of providers, prices and household costs will be reported. It will ensure consistency, and inflation rate adjustments will not be needed for cost calculations. The recommended treatment period will be seven days for inpatient treatment in the control arm and seven days for outpatient treatment in the intervention arm for RCT1. For RCT2, the average length of inpatient treatment is 48–72 hours, prior to a negative CRP laboratory test. In RCT2, the control group after randomisation will continue receiving inpatient care for five days, while the intervention group will be discharged from the hospital on oral amoxicillin for five days to be taken at home. Both arms will share the initial hospitalisation costs during the first two days in RCT2, including CRP test costs (including staff time, kits, and laboratory costs).The data on quantities used of injection gentamicin, injection ampicillin and oral amoxicillin will be as per the recommended treatment and partial treatment per SYI for each treatment arm under each RCT.The number of SYI receiving specific medicines and consumables for each arm under both RCTs will be calculated based on the numbers receiving recommended treatment and those receiving partial treatment.Information on types and quantities of consumables required with each medicine will be collected separately for each hospital and each arm under both RCTs. The cost of medicines and consumables will be charged per size in which they are dispensed. Medicine dosage varies with the weight of the YI [21,22]. Price will be taken for full strength, and the rest will be marked as wastage. Price data will be taken from the hospital's pharmaceutical department (if available); otherwise, the market price or the WHO price will be used.Data on annual financial expenditures and admissions in the newborn intensive care units or paediatric wards where YI with PSBI are treated as inpatients at the hospital will be collected and allocated based on patient days to calculate the inpatient bed costs/ SYI treated as an inpatient. These expenditures include administration, utilities, laundry, security, data management, internet, non-consumables and other costs in the hospital inpatient ward.Hospital ambulance to transport enrolled SYI under a specific treatment arm is a cost to the hospital. It is difficult to get this information separately for each enrolled SYI under different treatment arms from the hospital data. Indirect estimation based on the average trip cost and the number of SYI using free public ambulances, estimated from household data for each treatment arm in RCT1 and RCT2, will be used.Hospital data will also be collected for operational costs, which help to strengthen the assessment, identification, and treatment of SYI with PSBI. These include training, supplies, and communication. The total costs under these three will be estimated per SYI assessed. Staff training costs include the costs of development of training material and training cost per staff per day based on the per diems, honorarium for trainers, venue and refreshment costs. Total training costs will be calculated for all staff who were used to assess and treat SYI and will be estimated per SYI assessed. Training costs for research staff for outcome assessment or data collection will not be collected or included. Price and quantities of supplies used during the assessment, such as timers, thermometers and weighing scales, will be prorated for PSBI assessed. Communication costs, include job aids or educational material, and the cost of videos developed and played at the hospitals for educating the mothers about the danger signs. Data will be collected on item quantities and prices from hospitals to assess total costs and costs per SYI assessed.

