**Methods:**

Cost analysis will be conducted from societal (hospital and household) perspectives. Hospital medical costs (staff, medicines, and consumables) and operational costs (inpatient bed costs, non-consumables, training, and communication) will be collected through hospital surveys. Household costs, including medical payments for treatment (registration, consultations, medications, consumables) and non-medical costs (transport, food, and wage loss), will be collected through household surveys. In both RCTs, combined hospital and household (including medical and non-medical) costs for all randomised sick YIs (SYIs) will be used, with an intention-to-treat approach, to calculate the cost per SYI in each study arm. Effectiveness measures, based on the absence of adverse outcomes, will be used to determine incremental CE ratios and incremental net benefits. Separate societal and payer/provider perspectives will be considered, and site-specific willingness-to-pay thresholds will be estimated. The household’s medical and non-medical costs, along with their share of societal costs, will estimate the household burden per treated child.

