
### Estimation of hospital operational costs

Data collected for hospital indirect cost components – training, communications and supplies – are annual and relate to all infants assessed for PSBI during that year. For each site, expenses for training, communications and supplies will be added across facilities. The number of infants assessed during a year at a hospital will be estimated based on the total number of infants assessed over the entire study period and proportionally for 12 months. The sum of expenditures for each component will be weighted by the number of SYI assessed at each hospital for PSBI during the year to obtain the weighted expense per SYI at each site.Inpatient bed costs are shared costs across all infants and children admitted to newborn intensive care units and paediatric wards for shared items such as non-consumables, utilities, laundry, security, administration and other departmental expenses. The costs per admitted child will be estimated by dividing the total annual administrative expenditures (exclusive of staff costs, medicines, and consumables costs for enrolled SYI) of the paediatric and newborn intensive care units by the total number of children admitted in that year. These will be adjusted proportionately based on the average length of stay for enrolled SYI with PSBI relative to other SYI admitted during the year. We assume there are no inpatient bed costs for the intervention arm (outpatient) under RCT1 and for the 5-day ambulatory treatment in RCT2.Hospital transport/ambulance costs may be incurred for some patients brought to the hospital by public ambulance. Since it is difficult to obtain the data from the hospital database for each SYI enrolled, an indirect estimation method will be used. Household survey data will be used to determine the proportion of SYI who report using free public transport under different RCT treatment arms. Each site will calculate the average cost per trip based on the average distance to the hospital and the cost per km or mile. The cost per km depends on drivers' salaries, fuel costs for the average distance to hospitals in the study area, and vehicle maintenance costs at the site. Multiplying the average costs by the estimated number of SYI using public transport under each arm will provide an estimate of transport costs incurred at the hospital level.

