### CEA

CE will be evaluated by estimating the ICER, defined as the difference in mean costs between the intervention and control arms divided by the difference in effectiveness between the two arms: ICER = (C_1_ − C_2_) / (E_1_ − E_2_), where C_1_ are the average costs for the intervention group; C_2_ are the average costs for the control group; E_1_ is the mean effectiveness measure for the intervention group, and E_2_ is the mean effectiveness measure for the control group. We will use societal costs – hospitals and households’ – medical costs (staff time, medicines, consumables); hospital inpatient bed cost, operational costs and households’ non-medical costs (transport, food and wage loss) for ICER calculations for all randomised SYI in both arms. We will also report ICER from only the provider/payer perspective using only medical costs for all enrolled SYI and those receiving at least 80% of the recommended seven-day treatment as a sensitivity analysis [27].

For RCT2, while the baseline costs will be presented for both pre- and post-randomisation for both study arms, the costs for ICER calculations will be compared only post-randomisation.

For each RCT, cost measures will be evaluated in both the control and intervention arms for all enrolled infants who receive either the full seven-day treatment or partial treatment. Effectiveness will be assessed in the same population based on clinical outcomes recorded on days two (for RCT1), four, eight, and 15 following treatment initiation. The ICER will be calculated for each RCT to assess whether the intervention is more cost-effective than the control.

There can be 4 case scenarios for ICER (**Figure 2**):

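### Provider care after an early treatment failure is left uncosted on a rationale the plan itself contradicts, which biases the cost difference toward the arm with more early failures

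*Protocol article*

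**What the plan says.** All of the following is in the protocol article.

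- **Hospital data** separates infants who complete at least 80% of treatment from "those who receive <80% of seven-day (<5.5 days) treatment (partial treatment". On the causes of partial treatment it says: "The latter occurs due to a treatment failure, a change in treatment, readmission, left voluntarily, or death".
- **Costing of that group:** "For partial treatment, medical costs will be calculated for an average treatment period of three days in RCT1", and for two days after randomisation in RCT2. The arm mean is the average of full and partial cost, weighted by numbers of infants.
- **Exclusion:** "Costs due to complications, changes in treatment, and/or readmission are outside the seven-day recommended treatment window". The rule covers each arm of RCT1 and RCT2, and these costs go uncollected.
- **Estimation of hospital operational costs:** "We assume there are no inpatient bed costs for the intervention arm (outpatient) under RCT1". The same is assumed for the five ambulatory days in RCT2. No exception is stated for an infant admitted later.
- **Estimation of the household costs:** payments for non-recommended treatment are reported as an added burden, outside the cost-effectiveness analysis. Transport days and wage loss are capped at seven.
- **Outcomes and CEA:** poor outcomes include death up to day 15 (RCT1) or day 14 (RCT2) of therapy. The sensitivity analysis from the provider/payer perspective uses "those receiving at least 80% of the recommended seven-day treatment as a sensitivity analysis".
- **Abstract, Methods:** costs cover all randomised infants, "with an intention-to-treat approach, to calculate the cost per SYI in each study arm".

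**The concern.** The reason given for the exclusion fails for the group the plan has just defined. If a course stops before day 5.5 because treatment failed, was changed, or the infant was readmitted, then the event lies inside the seven-day window, and the care that follows begins there too.

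This matters because the main cost offset to outpatient care or early discharge is the care of infants who then do badly. In the incremental net benefit, λΔe − Δc, an early failure lowers Δe as it should. On the provider side of Δc it shortens the costed course and adds nothing for later care. The cost comparison therefore leans toward whichever arm has more early failures, and the results are meant to inform WHO guidance. Strengths and limitations does not mention the exclusion.

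**Working it through.** The article gives no figure for this effect, so there is none to reproduce. The steps below apply its costing rule.

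**1. Direction.** Let f be the share of infants with partial treatment.
- RCT1: mean costed days = 7(1 − f) + 3f. A partial course counts 3/7 = 43% of a full one.
- RCT2, after randomisation: 5(1 − f) + 2f. A partial course counts 2/5 = 40%.
- RCT1 at f = 5% gives 6.80 days; at f = 10%, 6.60 days. RCT2 at f = 5% gives 4.85 days.

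Mean day-based provider cost falls as f rises, in either arm.

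**2. Illustration in USD (RCT1).** The article's introduction cites USD 18.5 for outpatient treatment and USD 55 for hospitalisation from earlier studies. Assumptions of this review: these serve as unit costs, partial courses scale by 3/7, every failure is an early failure followed by one extra USD 55 stay, and control failures are 5%.
- Cost of a partial course: 18.5 × 3/7 = 7.93 (outpatient); 55 × 3/7 = 23.57 (inpatient).
- Control, plan's rule: 0.95 × 55 + 0.05 × 23.57 = 53.43. With later care: 53.43 + 0.05 × 55 = 56.18.
- Outpatient mean at failure share p, plan's rule: 18.5(1 − p) + 7.93p. With later care: add 55p.

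| Outpatient failures | Plan's mean | Mean with later care | Plan's saving | Saving with later care | Saving overstated by |
|---|---|---|---|---|---|
| 5% | 17.97 | 20.72 | 35.46 | 35.46 | 0% |
| 10% | 17.44 | 22.94 | 35.99 | 33.24 | 8.3% |
| 15% | 16.91 | 25.16 | 36.51 | 31.01 | 17.7% |

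The absolute overstatement is 55 × (p − 0.05): USD 0, 2.75 and 5.50.

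**3. Wider range, in units of one inpatient day.** Assumed: partial share 10–20% in the intervention arm against 5% in control; an outpatient day at 0.1–0.4 of an inpatient day; 3–7 inpatient days after failure.
- Example, RCT1, 10% against 5%, ratio 0.2, seven days. Plan's rule: 0.2 × 6.60 = 1.32 against 6.80, saving 5.48. With later care: 1.32 + 0.70 = 2.02 against 6.80 + 0.35 = 7.15, saving 5.13. Overstated by 6.8%.
- Over the whole range: about 2.5% to 32% in RCT1 and 3.5% to 52% in RCT2. The upper ends need 20% against 5% partial treatment.
- Equal shares and equal later care: no change in the difference, though both arm means are too low.

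**4. Does another part of the plan catch it?** The analysis of infants with at least 80% of treatment removes the early failures, so it cannot test how they were costed. The household survey catches part of the household cost, not the provider cost.

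**The case against.** Several points on the other side stand.

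- **Not every failure is costed short.** A failure first seen on day eight, or a death after at least 80% of treatment, is charged seven days and stays in the 80% analysis. Voluntary leavers and infants who die may truly have used a short course.
- **The cost of failure is not zero in the societal analysis.** Transport, food and wage loss over seven days enter it, as do household payments for the three study antibiotics, so part of the household cost of an in-window admission is counted, though only from a sample.
- **The rule is the same in both arms**, so the difference is biased only if early failures or later care differ between them.
- **The USD inputs are rough.** USD 18.5 is an Indian health-system figure and USD 55 an average over 14 countries and two perspectives. Scaling by 3/7 is too severe: initial assessment and operational costs are charged in full, and both RCT1 outpatient gentamicin days fall within the first three. This hardly moves the result. With no discount for partial courses, the 10% case gives 36.50 against 33.75, an overstatement of 8.1%.

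A reader might also infer that the analysis is not intention-to-treat. The text does not support that: the weighting keeps every randomised infant in the allocated arm. The fault is incomplete cost capture and a short cost horizon.

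None of this answers the contradiction or restores the missing provider cost.

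**Conclusion.** The point holds in a limited form. Three things are missing from the main ICER and net benefit: provider cost after early failure, household payments for non-recommended treatment, and all costs after day seven. The stated reason for leaving out complications, changed treatment and readmission is inconsistent with the plan's own definition of partial treatment. The bias runs toward the arm with more early failures.

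Its size cannot be known from the article, which gives no failure rates, no unit costs from these trials and no length of later care. On the assumptions in step 2 the outpatient saving is overstated by 0%, 8% or 18%.

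A reader might infer two stronger conclusions. One is that the outpatient mean is understated by 13%, 24% or 33% at 5%, 10% or 15% failures (2.75/20.72, 5.50/22.94, 8.25/25.16). That is arithmetically right for one arm on these inputs, but the ICER and net benefit use the difference between arms, where control failures offset part of it. The other is that proper costing would reverse the ranking. Nothing in the article supports this, and in every scenario in steps 2 and 3 the outpatient arm stays cheaper.

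**What to change.** 1. For each randomised infant with a failure, treatment change or readmission up to day 15, add inpatient provider cost: the site's derived cost per inpatient day times recorded days. Where days were not recorded, use an assumed stay shown over a range, for example 3 to 14 days.
2. Report the effect on incremental cost, ICER and net benefit, by site and pooled.
3. Add household costs only where the seven-day survey has not already captured them; otherwise they are counted twice.
4. Correct the rationale for the exclusion, state the cost horizon against the outcome horizon, and list any remaining exclusion as a limitation.
5. Keep the 80% analysis only as a description of completers.
6. Reconcile the costed days for partial treatment. Hospital data gives two post-randomisation days for RCT2 in one place and three days without naming a trial in another.

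The cost is analysis time. Data collection closed on 19 August 2024, and the article does not say that days of readmission were recorded, so part of the correction may rest on an assumed length of stay. That is why the range should be shown.

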### Framework for analysis

A common standardised protocol is being implemented across all study sites to ensure consistency in participant selection, interventions, and outcome assessments. The WHO coordinating team provides central training and oversight to harmonise activities, outcomes, and analytical procedures. All participating sites have extensive research experience, further supported by regular online and in-person meetings, data monitoring, and site visits by WHO monitors. The study started on 24 June 2021, and data collection was completed on 19 August 2024.

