
#### Household cost data

Household expense data will be collected during the last nine months of the study at each site to capture the out-of-pocket expenditures that households incur during the treatment of enrolled SYI under both treatment arms for RCT1 and RCT2. Data will be collected from at least 10% of SYIs enrolled under each arm at each site. These sampled households will be assumed to be representative of all treated YIs both temporally and geographically. Further, the household data for the seven-day treatment period will be collected either on day eight or 15 of the outcome visit or at most within two weeks from the last outcome assessment, to avoid recall bias. Where available, caregiver-reported expenditures will be cross-checked with receipts or facility payment records to enhance accuracy.Standardised household questionnaires will be used across all sites to collect data on medical and non-medical costs using the REDCap tool [25,26]. Training will be provided to collect data using these forms, and pilots will help improve the tool and data quality. Data inconsistencies will be identified, discussed with the sites and corrected at the analysis stage.Data will be collected on the type of treatment arm and duration of treatment. Direct treatment costs for each component will be collected in local currency from sampled households in each treatment arm for RCT1 and RCT2 at each site. Total medical expenses by households will be collected for registration and consultation fees, expenditures on medicines such as amoxicillin, ampicillin, gentamicin and other supportive care such as paracetamol, consumable supplies such as syringes, needles, canulas, bandages, spirits, gloves, laboratory expenses such as x-ray, blood work, urine tests (investigation costs), or any other payments to hospitals. Non-medical expenses, such as transport and food, will be recorded for seven days. Data will include the mode of transportation and expenses incurred by any household member on round-trip trips during the treatment period. Similar information will be collected on food, with the amount spent outside the home during the days the infant had to stay at or visit the hospital.Indirect expenses are opportunity costs, or the costs incurred by the household in terms of wage loss to take care of the sick child. Data will be collected from parents and caretakers who lost their wages due to time spent caring for the child. Household work that does not entail income will not be included in the opportunity cost. Data will be collected on the type of occupation/source of income, average earnings on a daily, monthly, or yearly basis (in the provided ranges), and the number of days not able to work to take care of the SYI. Maximum seven days of wage loss will be considered.

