All costs will be presented in 2024 USD. CE results will be interpreted in relation to country-specific willingness-to-pay thresholds and opportunity cost considerations. These findings will provide context-specific evidence to inform national policy decisions rather than relying on outdated GDP-based benchmarks [31].

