The analysis does not account for broader health system constraints, implementation barriers, capacity limitations, or informal healthcare costs that families may incur. The impact inventory focuses on direct effects within the healthcare sector and does not include impacts on other sectors. Factors such as supply chain inefficiencies and quality-of-care metrics specific to PSBI treatment are also outside the scope of this framework. In addition, research-related costs, including staff time for outcome assessment, monitoring and supervision, and protocol-specific training, will not be included.

The study period varies across hospitals and sites. While outcome data will be collected throughout the study, cost data will be collected during the final nine months. Although this may raise concerns regarding representativeness and recall bias, all cost data will be collected in local currency using a consistent price year, ensuring that salaries, medicine prices, and other treatment cost components remain constant for the defined price year.

Despite these limitations, this framework provides robust and policy-relevant evidence for evaluating cost-effective strategies to improve the management of PSBI in YIs in resource-constrained settings.

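### Household costs are labelled 2024 prices with no inflation adjustment, but every site's nine-month household window opens no later than about 19 November 2023

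*Protocol article*

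**What the plan says.** Under Hospital data, the article converts local currency at an average exchange rate that "will be for 2024, the period for which the salaries of providers, prices and household costs will be reported". It concludes: "It will ensure consistency, and inflation rate adjustments will not be needed for cost calculations". The Site-wise and combined analysis plan adds: "All costs will be presented in 2024 USD".

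The collection dates are given elsewhere. Framework for analysis: "The study started on 24 June 2021, and data collection was completed on 19 August 2024". Household cost data: "Household expense data will be collected during the last nine months of the study at each site". Strengths and limitations: "The study period varies across hospitals and sites".

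On the nature of the household amounts, Household cost data says: "Direct treatment costs for each component will be collected in local currency from sampled households in each treatment arm". Where possible, "caregiver-reported expenditures will be cross-checked with receipts or facility payment records to enhance accuracy". Interviews take place at the day 8 or day 15 visit, or within two weeks of the last outcome assessment.

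Strengths and limitations asserts one price year for all cost data and one recent financial period for provider and household data. It describes no step that would bring household spending to that year.

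**The concern.** The decision not to adjust for inflation rests on a factual premise, that household costs are 2024 costs. If some were incurred in 2023, they are 2023 local-currency amounts converted at a 2024 rate and labelled 2024 USD.

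A hospital can be asked for salaries or medicine prices for a chosen year. Transport, food and fees already paid cannot be collected that way: a receipt from December 2023 shows December 2023 prices.

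Household costs enter the societal cost per infant, the household share of that cost, the societal ICER and the site-level net benefits. If the price level of the household part depends on when a site closed and on local inflation, these figures are not on the common basis that the label claims, and pooling across sites mixes price levels.

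**Working it through.** **Inputs from the article**
- Data collection completed: 19 August 2024 (Framework for analysis).
- Household window: last nine months at each site (Household cost data).
- Declared price and exchange-rate year: 2024, no inflation adjustment (Hospital data).
- Site closing dates and inflation rates: not given.

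**Step 1. Can the stated premise be reproduced?** Window start = site closing date minus nine months. No site closes after 19 August 2024, so the latest possible start is 19 November 2023. Allowing two further weeks for late interviews (end 2 September 2024) moves the start only to 2 December 2023. A window wholly inside 2024 needs a closing date of about 1 October 2024, which the stated completion date rules out. The premise is not reproduced for any site. Spending also precedes the interview, which moves it slightly earlier still.

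**Step 2. Share of the window in 2023, for closure on 19 August 2024.** 19 November to 31 December 2023 is 12 + 31 = 43 days. The window, counting both ends, is 275 days. 43/275 = 15.6%, about 16%.

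**Step 3. Price gap for that closing date.** The article gives no inflation rate, so r is assumed at 5%, 10%, 20% and 30% a year, with smooth price growth and spending spread evenly over the window. Price level on a day relative to 1 July 2024 = (1 + r)^(days from 1 July 2024 / 365.25), averaged over days. As a hand check, the middle of the 2023 part is 10 December 2023, 204 days before 1 July 2024. At 30%, 1.30^(-204/365.25) = 0.864, or 13.6% low.

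| Assumed inflation | 2023 days: below mid-2024 | Whole window: below mid-2024 | Part of the whole-window gap due to 2023 days |
|---|---|---|---|
| 5% | 2.7% | 1.2% | 0.156 × 2.7 = 0.4 points |
| 10% | 5.2% | 2.3% | 0.156 × 5.2 = 0.8 points |
| 20% | 9.7% | 4.2% | 0.156 × 9.7 = 1.5 points |
| 30% | 13.6% | 6.0% | 0.156 × 13.6 = 2.1 points |

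The last column matters for reading the result. At this closing date, most of the 1% to 6% arises because the window's 2024 days are mostly before mid-year. A convention that treats all of calendar 2024 as one price year would leave only the last column.

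**Step 4. Earlier closing dates (hypothetical).** At a site closing on 31 March 2024, about 67% of the window falls in 2023, and the window average is about 3% to 15% below mid-2024 at 5% to 30% inflation. At a site closing on 31 December 2023 the share is 100% and the gap about 4% to 20%. The article does not show that any site closed on these dates.

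**Step 5. Effect on the comparison of arms.** Both arms are surveyed in the same window at each site. If household spending in both is scaled by the same factor f, the household cost difference becomes f × (difference). Its size changes and its sign does not. Across sites f can differ, which is where comparability is lost.

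**The case against.** The strongest defence has four parts.

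1. **The effect is small.** At the only closing date documented, the gap is a few per cent even under high assumed inflation. It is probably minor beside the purposive sample of roughly 10% to 15% of infants, which the article discloses together with the late collection of cost data. This stands as a point about size. It does not rescue a statement whose premise is false.

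2. **There is no bias between arms.** Correct, for the reason in Step 5.

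3. **Hospital costs may come from the same period.** A reader might infer that household costs are understated relative to hospital costs. The article does not support that. Bed and operational costs come from annual expenditures whose year is not stated, and the limitations section places cost data in general in the final nine months. If hospital inputs share the period, the distortion of the household share largely disappears.

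4. **Wage loss is coarse.** Earnings are recorded in ranges and the middle of the range is used, so indexing this component adds little real precision. This is fair for wages and does not apply to transport, food and fees.

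The statement of a consistent price year does not answer the point, because no procedure is attached to it. Nor is this a detail left to a fuller document: the article decides the matter and gives its reason.

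**Conclusion.** The point holds in a limited form. The article rules out inflation adjustment on the ground that household costs are 2024 costs, and its own dates show that the planned household window opens no later than about 19 November 2023 at every site. For closure on 19 August 2024, about 16% of the window is in 2023 and the window average is about 1% to 6% below mid-2024 prices. This assumes 5% to 30% annual inflation, smooth price growth and evenly spread spending.

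The consequence is a rescaling of household costs and of the household part of incremental cost, with reduced comparability across sites. No ICER or net-benefit conclusion has been shown to change.

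Three stronger readings are not supported:
- **A 5%, 13% or 23% understatement** (1 − 1/1.05, 1 − 1/1.15, 1 − 1/1.30) needs a full year's gap. At the documented closing date the 2023 days centre on little more than half a year before mid-2024.
- **Half or all of a site's window before 2024** needs closing dates that are not given. The remark that study periods vary could reflect start dates as well as end dates.
- **Every window opening in 2023** is too exact. The dates show only no later than November 2023; a site that closed before about October 2023 would have opened its window in 2022.

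**What to change.** Delete the statement that inflation adjustment is not needed. In its place, state that household amounts incurred before 2024 are restated in 2024 local prices with the national consumer price index, using the treatment or interview date of each record, and then converted at the 2024 average exchange rate. State the year of each hospital expenditure input and apply the same rule to any year other than 2024. State also whether 2024 prices means the calendar-year average or a single reference date, since at late-closing sites that choice accounts for much of the remaining gap.

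At minimum, report the true price period for household costs with site closing dates, and present the restatement as a sensitivity analysis on societal cost, the household share, the ICER and net benefit.

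The cost is one multiplication per dated household record, a public index for six countries and a change of wording. The small downside is reliance on a national index, which is approximate for wages recorded in bands.
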